#### Infants’ salivary cortisol

Salivary samples will be collected twice, before (baseline) and after (response) a heel stick, which is part of routine care. One hour before the heel stick, the infants will not be fed. One sample will be collected just before the heel stick, and the other will be collected 20 to 30 min after completion of the blood draw. Saliva is collected using a Salivette® Cortisol (Sarstedt, Numbrecht, Germany). After collection, samples will be centrifuged at 4000 rpm for 15 min. Afterward, they will be frozen at − 40 °C until analysis. All the samples will be safely stored in the laboratory of the hospital. Salivary cortisol levels will be determined using the quantitative cortisol enzyme-linked immunosorbent assay (ELISA) Kit (R&D Systems, Inc. Minneapolois, MN, USA), which is specifically designed for research purposes with a high sensitivity of 0.111 ng/mL, which allows the measurement of low concentrations of cortisol. Samples will be run in duplicate, and all samples from each individual will be run in the same assay.

#### Premature Infant Pain Profile

The PIPP is a pain scale originally developed to assess procedural pain in preterm neonates [64]. This profile consists of seven items, including three behavioral indicators (brow bulge, eye squeeze, and nasolabial furrow), two physiological indicators (heart rate and oxygen saturation), and two contextual indicators (GA and behavioral state). Each indicator is evaluated on a 4-point Likert-type scale. Total scores range from 0 to 21, reflecting minimal to severe pain level. The construct validity and internal consistency of the PIPP have been well established [65]. Behavioral indicators will be recorded by camera, and physiological indicators will be collected via pulse oximeter. The infants’ GA will be retrieved from the medical records.

All digital video files will be independently analyzed by two researchers after they are mixed to ensure data blindness.

#### Infant Neurological International Battery

The INFANIB is used as a screening tool to assess infants’ neurodevelopmental status at term-equivalent age (40 weeks of corrected age). This instrument was established by Ellison and Browning in 1985 and was designed to detect gross motor developmental delay and, it was hoped, to predict later neurological dysfunction during the first 18 months of life [66]. Evidence shows that the INFANIB is an appropriate neurological outcome test for premature and/or LBW infants [67–69].

#### Magnetic Resonance Imaging (MRI)

Quantitative MRI will be used to observe preterm infants’ brain growth at term-equivalent age. Total cerebral volume, volumes of white and gray matter, and the cerebral cortex will be measured to predict brain development in preterm infants.

4.1.4.1. MRI data acquisition

MRI examinations will be performed with a 1.5 T magnet (Siemens Medical Systems, Berlin, Germany) equipped with an eight-channel phased array head coil. The following sequences will be acquired for all subjects: (1) standardized T1-weighted and T2-weighted images; (2) magnetization prepared rapid acquisition gradient echo (MPRAGE) images obtained using the following parameters: 144 slices, TR = 2300 ms, TE = 3.39 ms, slice thickness = 1 mm, flip angle = 7°, inversion time = 1100 ms, FOV = 200 × 256 mm^2^, and in-plane resolution = 200 × 256; (3) blood oxygen level-dependent (BOLD) images obtained using the following parameters: 24 axial slices, thickness/gap = 5.0/0 mm, in-plane resolution = 64 × 64, TR = 2000 ms, TE = 30 ms, flip angle = 90°, and FOV = 210 × 210 mm^2^.

Pulse oximetry and heart rate will be monitored throughout the intervention. Ear protection will be used for each infant (MACK’S Earplugs, McKeon Products, Inc., Warren, MI, USA; MiniMuffs, Natus Medical, San Carlos, CA, USA). Chloral hydrate (25–50 mg/kg) will be administered to infants.

### Secondary outcomes

#### Infants’ safety and physiological stability

Safety will be measured by the incidence of hypothermia (< 36.5 °C) and apnea of any duration accompanied by desaturation (SpO_2_ < 88% in room air). Infants’ physiological stability, such as respiratory rate (respiratory rate < 60/min), heart rate (100 beats/min to 180 beats/min), and oxygen saturation (SpO_2_ > 90%) variables, will be recorded during SSC and throughout hospitalization.

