According to the definition of KC, the mother is the optimal provider for SSC, to promote breastfeeding. However, in China, women are encouraged to stay at home and to rest completely for 1 month after birth (called “doing the month”) for recovery [43]. These traditional postpartum practices are accepted regardless of a woman’s age and education [44]. This resting period results in mothers not being able to perform even one or a few hours’ session of SSC per day after discharge from the hospital, which will greatly delay mother-infant exposure in the first month. In this case, father-infant SSC is an optimal alternative.

Whereas most studies focus on the effects of maternal-infant SSC, few studies have researched the father’s participation in SSC. Ludington-Hoe et al. and Erlandsson et al. found that infants who received father-infant SSC maintained higher skin temperature and had better state behavior responses [45, 46]. In addition, no negative effects were observed on the metabolic rate and energy balance in performing paternal SSC [47, 48]. Evidence also suggested that, to some extent, father-infant SSC was capable of decreasing pain response in preterm infants [49–51]. Infants who received KC cried less, and fathers communicated more vocally not only with the newborn but with the mother. Fathers who provided SSC were more willing to be involved in infant care [52], which established bonding and attachment [53] with the infant and created a more stimulating, more harmonious, and generally better family environment [54] beneficial for infant development [23]. Qualitative studies also reported that fathers felt grateful for being needed; they also felt more included in the process, which facilitated their attainment of a paternal role and achievement of equal parenthood [55–58].

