### Inclusion criteria:

GA between 32^0^ and 34^6^ weeks with BW ≥ 1500 gApgar scores at 1 min and 5 min ≥ 7Vaginal or caesarean deliveryMedically stable for 24–72 h (definition of stability is based on the infant’s vital signs, with temperature ranging from 36.5 to 37.5 °C, SpO_2_ > 90%, respiratory rate < 60/min, heart rate of 100 beats/min to 180 beats/min)

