### Intervention group

Infants in the intervention group will be offered SSC as soon as they are stable (approved by a pediatrician in the unit), and they are expected to receive SSC every day during hospitalization. SSC will be performed between 4:00 pm and 6:00 pm for at least 1 h in a private room adjacent to the unit with an ambient temperature between 22 and 24 °C and appropriate light and sound levels. Fathers will wear a comfortable gown and be seated on a reclining chair at an angle of 40 to 60°. Each infant will be taken out of the incubator, unclothed (only diaper and cap are kept on), and placed in an upright position on the father’s chest. The infants will be covered by a blanket to keep them warm. Fathers will be educated on how to hold the infant correctly and encouraged to watch their child and talk to them. Father and baby will be left in the kangaroo position for at least 1 h. During SSC, infants will remain attached to a cardiorespiratory monitor and will be observed by a nurse; routine nursing including parenteral nutrition administration and IV injection can also be performed. Because SSC is not routine care in our hospital, this practice will follow the World Health Orgainization (WHO) guidelines [63].

If hypothermia or apnea of any duration accompanied by desaturation occurs during the SSC, the intervention will be discontinued, and the eligibility of the infant will be reassessed. Infants in the intervention group will receive the same standard treatment as infants in the TC group except for at least 1 h of SSC every day.

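### Temperatures above the protocol's own 37.5 °C upper limit enter no defined safety or stability outcome

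*Protocol article*

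**What the plan says.** All places are in the protocol article.

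- **Inclusion criteria.** Medical stability is defined by four vital signs. Temperature has two limits: "temperature ranging from 36.5 to 37.5 °C". The others are "respiratory rate < 60/min, heart rate of 100 beats/min to 180 beats/min" and an SpO2 above 90%.
- **Secondary outcomes, Infants' safety and physiological stability.** The safety measure is "Safety will be measured by the incidence of hypothermia (< 36.5 °C) and apnea of any duration accompanied by desaturation". Three stability variables follow, each with the limits it has at entry: breathing rate, pulse and SpO2. The last of them reads "oxygen saturation (SpO_2_ > 90%) variables, will be recorded during SSC and throughout hospitalization". Temperature is not among the three.
- **Background.** On earlier studies of fathers, the article reports that "infants who received father-infant SSC maintained higher skin temperature".
- **Intervention group.** The infant lies on the father's chest, and "The infants will be covered by a blanket to keep them warm".
- **Secondary objectives.** Safety and physiological stability of father-infant SSC come first in the list.
- **Data collection.** Temperature is among the clinical data recorded during hospitalization, as are adverse events.

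**The concern.** The article sets its own upper limit for a stable temperature and then does not use it when it defines the outcomes. A safety comparison built on the outcome section can show whether SSC makes infants cold. It cannot show whether SSC takes them above the range that the same article calls stable. The Background gives a reason to look at that side, because the effect it reports for father-infant SSC is a higher skin temperature.

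At stake is what the trial may conclude about thermal safety. The Discussion says the data may be used to promote paternal SSC and to modify guidelines. A statement that SSC is thermally safe would rest on a count of low readings only.

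**Working it through.** The article gives no figure for this point, so there is nothing to reproduce. The check compares definitions.

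**Step 1: set the two sections side by side.**

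| Vital sign | Stable at entry (Inclusion criteria) | Outcome section |
|---|---|---|
| Respiratory rate | < 60/min | < 60/min, stability variable |
| Heart rate | 100 to 180 beats/min | 100 to 180 beats/min, stability variable |
| SpO2 | > 90% | > 90%, stability variable |
| Temperature | 36.5 to 37.5 °C | < 36.5 °C is a safety event; no upper limit; not a listed stability variable |

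Three of the four signs carry over unchanged. Only temperature loses a limit.

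**Step 2: apply the outcome section as written.** Take infants whose other signs are normal (respiratory rate 45/min, heart rate 150 beats/min, SpO2 96%, no apnea). These values are chosen only to isolate temperature.

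| Temperature | Within entry band? | Safety event? | Outside a listed stability limit? |
|---|---|---|---|
| 36.4 °C | No | Yes | No |
| 38.0 °C | No | No | No |

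Both infants fall outside the entry band. Only the cold one enters a defined outcome.

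**Step 3: look for another route.** The Adverse events section names hypothermia, hypoglycemia and physiological instability, and does not define the last. Data collection records temperature and any adverse event. A high reading could therefore be reported, but only if someone judges it to be an adverse event. No stated rule makes it a count to be compared by arm.

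**Result.** Among the defined outcomes, no reading above 37.5 °C is counted on account of temperature.

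**The case against.** The strongest reply has three parts.

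1. *The stability list is illustrative.* The three variables are introduced as examples and are said to be recorded, with no explicit scoring rule. Since their limits repeat the entry definition, one may read the temperature band as carried over too. This is possible but not stated. The same paragraph gives temperature its own treatment, with a lower limit only, and that speaks against an implied upper one.
2. *High readings are not lost.* Temperature and adverse events are collected, and fuller adverse-event definitions may stand in a full protocol that is not shown. This stands in so far as the data should exist. It does not make high readings part of the safety outcome, which the article defines by named events and a numeric cut-off.
3. *Cold is the harm the authors expect.* The infant leaves the incubator with little clothing, in a room at 22–24 °C. Hypothermia is named as a possible adverse event and as a reason to discontinue SSC. This stands.

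The third part also answers a stronger reading. A reader might infer that counting only cold infants favours SSC by construction. The article does not support that, because the event it counts is one it treats as a risk of SSC.

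A reader might also extend the point to breathing, since the respiratory rate limit has no lower bound. That does not hold up. The limit is the same in both sections, heart rate is bounded on both sides, and apnea with desaturation is a safety event. Nothing in the article says that SSC slows breathing. Whether apnea without desaturation should count is a design choice, not an inconsistency.

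**Conclusion.** The point holds for temperature. The Inclusion criteria set an upper limit of 37.5 °C for a stable infant, and the outcome section drops it. High readings therefore belong to no defined safety or stability outcome, and only an undefined adverse-event route remains.

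The conclusion rests on reading the outcome section as written, without an unstated carry-over of the entry band. It does not assume that SSC causes overheating. The Background reports higher skin temperature without a size, and the outcome section names no measurement site. A reader might want an expected share of readings above 37.5 °C, but it would depend entirely on an assumed mean, spread and shift, so none is given.

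The effect is confined to one secondary objective and to what may be said about thermal safety. The primary outcome, the sample size and the main analysis are untouched.

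**What to change.** Reconcile the Inclusion criteria and the outcome section for the purpose of counting outcomes. In Infants' safety and physiological stability, state that temperature readings outside the protocol's own 36.5–37.5 °C band will be reported by arm, with readings below 36.5 °C and readings above 37.5 °C shown separately. Use the temperatures already listed under Data collection.

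This uses a limit the article already contains. It proposes no new clinical threshold and does not touch the rule for discontinuing SSC.

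Cost: a wording change and one more row in the safety table, which may look less favourable to SSC. The article does not say how often temperature is taken in each arm. An arm measured more often has more chances to record a reading outside the band, so the number of readings per infant should be shown by arm beside the counts.

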## Abstract

**Background:**

Skin-to-skin contact (SSC) is an evidence-based intervention that benefits low birth weight /preterm infants. However, China’s health institutional policy inhibits parents from visiting their baby in the neonatal intensive care unit (NICU). In addition, the Chinese traditional postpartum behavioral practice of confining women to home raises barriers to mother-infant contact. Thus, to shorten the duration of parent-infant separation, father-infant SSC is considered a possible alternative. This study determines whether it is safe to perform father-infant SSC in the NICU and investigates how paternal SSC affects outcomes compared with traditional care (TC) for moderately preterm infants.

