Although it remains unclear whether SSC has long-lasting effects on preterm infants in terms of neurodevelopmental outcomes, studies show that KC may have a direct effect on infant neurophysiological organization [23]. Long-term follow-up studies have found that KC preterm infants show attenuated stress responses, have organized sleep and better cognitive control, and maintain long-lasting social and behavioral protective effects even after 10 and 20 years [36, 37].

KC has been recognized as an evidence-based intervention to improve health outcomes for LBW/preterm infants; however, it is not common in China. According to the national policy in China, parents are not allowed to enter the NICU to stay with their infants. Parent-infant separation begins after delivery until the infant is discharged, which accounts for a long period of time. This model of NICU care is accepted because it avoids the incidence of infection and also because of the ease of managing the patients. For severely ill infants, one of the preventive measures is to reduce the incidence of infection, which should be addressed by professionals. However, for medically stable preterm infants, a meta-analysis showed that LBW infants who received KC had reduced incidence of mortality, nosocomial infection, and severe illness compared to those who did not receive KC [38]. These results also support the idea that parents entering the NICU wards did not increase the risk of LBW infants becoming infected [38, 39]. Furthermore, the concept of family-centered care (FCC), which allows parents to participate in taking care of the baby, has been increasingly considered an important component of the NICU [40]. Evidence shows that FCC is feasible and safe, and it does not increase the rates of nosocomial infection; the incidence of necrotizing enterocolitis (NEC) was significantly lower in the FCC group in previous studies [41, 42]. These results indicate that allowing parents to visit their infants and perform SSC with adequate hygiene practice is safe, and it could be applied in Chinese NICUs.

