As mentioned previously, premature birth can be stressful and traumatic for parents and can cause negative consequences for the natural establishment of the parent-infant relationship. The NICU environment interrupts parental involvement in caring for the infant and jeopardizes the process of attachment between parents and infant. It is recognized that fathers play an important role in the care of their children. Positive father-child interactions established at an early age have been shown to reduce cognitive delay in infants [59]. A father’s involvement is associated with improved cognitive outcomes in preterm infants, which may suggest a possible intervention [60]. Studies show that fathers of preterm infants often feel stressed [61], overwhelmed, isolated, and out of control [62]. Parental psychological well-being and parent-child interaction may affect infants’ development outcomes. However, these negative feelings appeared to be relieved by offering SSC, as fathers reported feeling in control and at ease when they were more involved in caring for their infants. By providing SSC, fathers consider themselves an important part in the course of caring for infants through physical closeness [55].

The aim of the present study is to investigate whether paternal SSC is safe and how it affects outcomes for moderately preterm infants born at GA 32^0^–34^6^ weeks. We hypothesize that the practice of father-infant SSC in the NICU is feasible and will benefit both infants’ and fathers’ well-being.

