### Control group

Conversely, infants in the TC group will be cared for under radiant warmers or in the incubators and treated with routine nursing procedures. These infants will not receive any paternal SSC during hospitalization.

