### Adverse events

This study will be implemented under thorough assessment and close monitoring by the medical staff. Although negative effects are rare, there is a chance that infants may have hypothermia or hypoglycemia or experience physiological instability during SSC. If negative effects occur, SSC will be discontinued, and the infants will be reassessed by medical staff.

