### Data collection, management, and analysis

#### Data collection

Two researchers will collect the data, which will be kept in a locked cabinet in the NICU. The data are accessible only by the researchers. The following clinical data will be collected: (1) parents’ and infants’ demographics, collected from the medical record; (2) infants’ condition during hospitalization: daily weight, head circumference, temperature, oxygen saturation and heart rate, total amount of enteral and parenteral nutrition given, any sepsis or infection, NEC, duration of antibiotic, biomedical, ultrasound, X-ray and any other test results, any adverse events; (3) observation of SSC: time and frequency of SSC, any cause for interruption or termination of SSC, adverse events; (4) the online STAI and PPAS questionnaires, sent to the fathers’ telephones, with the completed data collected and securely stored by the SoJump online survey software.

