However, fathers can also perform KC for infants, whether in the hospital or after discharge. According to the definition of KC, the mother is the optimal provider of KC because SSC between mother and infant is the basis of early successful and exclusive breastfeeding [77, 78]. Nevertheless, the father and even other family members are suggested to perform KC while the mother is not available. Evidence shows that the father plays a significant role in infant care. Findings from previous studies show that fathers who provide SSC induce pain alleviation, paternal-infant attachment, and family bonding and create a more harmonious caregiving environment [55, 57, 79, 80], which can be beneficial to infants’ development. However, studies on fathers providing SSC remain limited in China; thus, the effects of paternal SSC on both preterm infants and fathers have not been well studied.

This study aims to investigate the safety and effects of paternal SSC on neurodevelopmental outcomes in preterm infants. The data gathered in this study can be used to promote the implementation of early paternal SSC in the NICU and modify guidelines and procedures to facilitate the involvement of fathers in caring for their preterm babies when mothers are absent.

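### The declared safety measure leaves out infection, a harm the protocol itself gives as a reason for keeping parents out of the NICU, although the data are already collected

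*Protocol article*

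**What the plan says.** Safety is a stated purpose of the trial. The abstract says: "This study determines whether it is safe to perform father-infant SSC in the NICU". The last paragraph of the Background repeats that the aim is to "investigate whether paternal SSC is safe", and safety with physiological stability is the first secondary objective.

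Under Secondary outcomes, the section on infants' safety and physiological stability gives the measure: "Safety will be measured by the incidence of hypothermia" (below 36.5 °C) and of apnea with desaturation (SpO2 below 88% in room air). It adds respiratory rate, heart rate and oxygen saturation as physiological stability, recorded during SSC and through the hospital stay. Infection is not there, not among the possible harms in the Adverse events section, and not among the other primary or secondary outcomes.

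On the existing policy of keeping parents out, the Background says: "This model of NICU care is accepted because it avoids the incidence of infection". Ease of managing patients is the second reason given. The Background then cites earlier studies in which infection did not rise with kangaroo care or family-centered care.

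The Data collection section lists, for the infants' condition during hospitalization, "any sepsis or infection, NEC, duration of antibiotic", along with any adverse events. The Data analysis section specifies intention-to-treat and a Pearson chi-square or Fisher's exact test for categorical variables. The Discussion says the results "can be used to promote the implementation of early paternal SSC in the NICU".

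**The concern.** The two declared safety events are acute ones. They answer whether an infant stays warm and keeps breathing adequately. They do not answer the question that the protocol itself attaches to the current policy, which is whether letting a parent into the unit brings infection with it.

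If the results are used to argue for changing that policy, a statement that paternal SSC is safe would, on the declared measure, be silent on infection. The opposite risk also exists. Infection is recorded but is not a declared outcome, so the trialists could decide whether to feature it after seeing how it came out. Either way, readers could not tell a planned safety result from a chosen one.

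**Working it through.** **Where infection appears in the protocol article**

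| Place | Infection named? |
|---|---|
| Background | Yes, as a reason for the no-parent model; earlier evidence of no increase is cited |
| Primary outcome measure | No |
| Secondary outcomes, safety and physiological stability | No |
| Other secondary outcomes (state, anxiety, attachment) | No |
| Adverse events | No |
| Data collection | Yes: sepsis or infection, and NEC |
| Data analysis | Not named, but the general categorical rule would cover it |

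Infection is therefore collected and analysable, but not declared as an outcome.

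**The one planned figure that matters here: 25 per arm.** Inputs from the Sample size section are means 0.21 and 0.57, SDs 0.12 and 0.61, two-sided 5%, 80% power.
- Pooled SD = √((0.12² + 0.61²)/2) = 0.440.
- Standardized difference = (0.57 − 0.21)/0.440 = 0.819.
- Two-sided t test power is 0.793 at 24 per arm and 0.810 at 25, so 25 per arm reproduces. It rests on cortisol; no figure is given for safety.

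**What 25 per arm can say about infection.** The document gives no infection rate, so the counts below are assumptions. For equal counts x in each arm, p = x/25. The Wilson 95% limits (l, u) for each arm give the Newcombe half-width √((p − l)² + (u − p)²).

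| Events per arm | p | Wilson l, u | Half-width (percentage points) |
|---|---|---|---|
| 1 | 0.04 | 0.007, 0.195 | 15.9 |
| 2 | 0.08 | 0.022, 0.250 | 17.9 |
| 3 | 0.12 | 0.042, 0.300 | 19.6 |

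For x = 1: √((0.040 − 0.0071)² + (0.1954 − 0.040)²) = √(0.0011 + 0.0242) = 0.159.

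**Power for a doubling**, two-sided Fisher's exact test at 0.05, 25 per arm, summed over all pairs of binomial counts (assumed rates, traditional care vs SSC):
- 5% vs 10%: 1.3%
- 10% vs 20%: 8.6%
- 15% vs 30%: 15.0%

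Even with no infections in the SSC arm, the two-sided exact upper 95% limit for its rate is 1 − 0.025^(1/25) = 13.7%.

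Infection can be estimated in this trial, but an increase cannot be ruled out with any precision.

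**The case against.** The authors had reasons for their choice. The Background links infection prevention chiefly to severely ill infants, then turns to stable preterm infants and cites a meta-analysis with less nosocomial infection under kangaroo care, and family-centered care studies with no increase in nosocomial infection and less NEC. The trial enrols only stable infants, excludes ventilated ones, and holds SSC in a private room beside the unit. Acute instability is a sensible focus. This stands as a justification for running the trial. It does not measure infection in this hospital, where parental entry is the departure from practice.

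A second objection is that the trial is too small for infection to be informative. The figures above confirm that. It is a reason to limit the conclusion, not to leave the harm out of the safety definition.

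A third is that a condensed article leaves such detail to the full protocol or analysis plan. An operational case definition of sepsis or NEC may well be found there, and its absence here is no fault. But the article does not leave the safety measure open; it names the events and their thresholds.

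A reader might also infer more than the text supports:
- *That infections would go unrecorded.* They would not; the Data collection section lists them.
- *That the time window and the analysis are open.* Collection is stated to be during hospitalization, and intention-to-treat and a categorical test are given. Counting from randomization only refines the start.
- *That the safety measure biases the comparison.* Nothing suggests this; the definitions and data list apply to both arms.
- *That hypoglycemia is a parallel gap*, since the Adverse events section says "there is a chance that infants may have hypothermia or hypoglycemia or experience physiological instability during SSC". It is treated there as an adverse event, and any adverse events are collected, so it adds no weight.

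**Conclusion.** The point holds in a limited form. The declared safety measure omits infection, although the protocol names it as one reason for the existing policy, makes safety an aim, and already collects the data. What is missing is the status of infection as a safety outcome. Without it, a conclusion of safety can be drawn with infection left out, or infection can be brought in selectively.

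The gain from declaring it is modest: a pre-specified descriptive estimate and a safety conclusion limited to what the data support. With 25 per arm the 95% interval for the difference would be about ±16 to ±20 percentage points for one to three events in each arm, and power for a doubling would be 1.3% to 15.0%, on assumed counts and rates. A reader might infer that declaring infection would let this trial show that paternal SSC does not raise it; at this size it would not. The primary outcome and the sample size are unaffected.

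**What to change.** Add infection (sepsis or other infection) and NEC to the outcomes in the section on infants' safety and physiological stability, counted from randomization to discharge. Use one clinician-set definition in both arms, agreed before the arms are compared and applied to the data already listed under Data collection.

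Report the number of infants affected per arm and the difference with a 95% CI, labelled descriptive. State in advance that a non-significant difference will not be reported as no increase in infection, and word any conclusion on safety by what the interval excludes.

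The cost is wording in the protocol and registry entry, plus agreement on the definition. N stays at 50 and no new data are needed. The price is a wide interval in the report and a more limited safety claim.
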